##### **14.4.2 Laboratory tests, vital signs**

Vital signs and quantitative laboratory test results, including heart rate variability, will be presented as descriptive statistics before and after administration for each herbal preparation group. Changes will be compared between groups using the independent two-sample t-test or Wilcoxon rank-sum test. Within-group changes will be tested using the paired t-test or Wilcoxon signed-rank test. Additionally, laboratory test results before and after administration will be categorized as normal (including clinically insignificant abnormal) or clinically significant abnormal changes. Changes within groups will be tested using McNemar's test (or McNemar's exact test).

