#### **Laboratory Tests, Vital Signs**

Present descriptive statistics for pre- and post-intervention values and changes in vital signs and quantitative laboratory test results for each group. Compare changes between groups using the independent two-sample t-test or Wilcoxon rank-sum test, and changes within each group using the paired t-test or Wilcoxon signed-rank test. Additionally, present contingency tables for dichotomous laboratory test results and ECG results showing changes from pre- to post-intervention categorized as normal (including clinically insignificant abnormal) or clinically significant abnormal. Test changes within each group using McNemar's test (or McNemar's Exact test).

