### 3) Number of Subjects and Rationale

This study is a prospective pilot investigator-initiated clinical trial. The results obtained from this study will be used to calculate the number of participants for future confirmatory clinical trials. A total of 100 subjects will be recruited, with 50 in the treatment group (receiving Kyung-Ok-Go) and 50 in the control group (receiving placebo).

| Institute                                       | Treatment group | Control group | Sum |
|-------------------------------------------------|-----------------|---------------|-----|
| Kyunghee University
Korean Medicine Hospital | 30              | 30            | 60  |
| Dongueui University
Korean Medicine Hospital | 20              | 20            | 40  |
| Sum                                             | 50              | 50            | 100 |

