### **11.3 Blinding, etc.**

At Visit 0, each subject will be assigned a unique screening number by the researcher. This number will begin with CVS1-01 at Kyung Hee University Korean Medicine Hospital and CVS2-01 at Dong-Eui University Korean Medicine Hospital, and will be assigned in ascending order from the smallest available number. Once assigned, the screening number will not be reused. If a subject is not treated at Visit 1 for any reason, the screening number assignment and the reason for non-treatment will be documented in the Screening Log and the case report form (CRF).

Block randomization will be employed, and the block size will not be disclosed to maintain blinding. An independent statistician will generate random numbers using STATA Version 4.2 (StataCorp LLC., Texas), and these numbers will be sent to the labeling site for the IMPs, where they will be labeled and packaged in the order of randomization. This ensures both the researcher and the subjects are blinded. The probability of allocation to the treatment or control group is 1:1.

To ensure allocation concealment, the IMPs packaged according to the random numbers generated by the independent statistician will be delivered to the trial sites. Subjects who meet the inclusion criteria, do not meet the exclusion criteria, and voluntarily consent in writing will be assigned the lowest available random number in the order of their participation. This number will be recorded in the CRF, and the IMP will be dispensed accordingly.

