### **11.4 Observation and inspection items**

#### **1 1.4.1 Clinical trial progress schedule**

##### **11.4.1.1 Visit 0 ( screening visit)**

Participants who apply to join this clinical trial will receive an explanation of the study and then undergo the following tests. Screening tests can be repeated once within the screening period and must be completed before assigning a participant number. If a retest is conducted, the suitability for participation is determined based on the retest results, and the investigator should document the reasons for the retest, the basis for the decision, and the final results in as much detail as possible.

- ① Before enrolling a clinical trial participant, the principal investigator or the person in charge explains the study process and obtains written consent from the participant.
- ② Screening numbers and random assignment numbers are assigned in the order of written consent completion.
- ③ Investigate and record whether the participant is involved in other clinical trials (within the last 30 days), demographic information, medical history (including diabetes), COVID-19 information (date of onset, recovery date, vaccine details including date, manufacturer, doses, and side effects), past fatigue-related history, and current fatigue symptoms. Even if the participant is receiving diabetes treatment, they can join the study if their test results are within controlled ranges (HbA1c within normal range).
- ④ The physical exam covers general condition, nutritional status, skin/mucosa, eyes (excluding vision impairment), ENT, thyroid, lungs, cardiovascular system, abdomen, renal/urinary system, neurological/psychiatric system, spine/extremities/tumors, peripheral circulation, and lymphatic system.
- ⑤ If possible, confirm and document COVID-19 infection status through the following:
  - SMS notifications from the Disease Control and Prevention Agency regarding confirmed cases.
  - Medical records and diagnostic certificates from the time of COVID-19 diagnosis and treatment.
  - PCR test records from the time of diagnosis.
  - Certificates related to COVID-19 diagnosis or release from quarantine issued by public institutions.
- ⑥ Verify current medications.
- ⑦ Measure vital signs.

- ⑧ Conduct an electrocardiogram (ECG) test.
- ⑨ Collect blood samples for laboratory tests and immune and metabolite analysis (laboratory test results within 28 days of the screening visit can be used):

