## 14. Statistical Analysis Methods

### 14.1 General principles of result analysis

The primary analysis for efficacy evaluation will use the Full Analysis Set (FAS). Safety evaluations will be conducted using the Safety Set. All statistical tests will be two-sided with a significance level of 5%. For efficacy evaluation, missing data in the FAS will be handled using the Last Observation Carried Forward (LOCF) method for statistical analysis, while all other data will be analyzed as originally recorded.

**Safety Set (SS):** A group of subjects who have received the investigational medicinal product at least once and have undergone at least one safety-related follow-up.

**Full Analysis Set (FAS):** A group of subjects who, in accordance with the ITT principle, have received the investigational medicinal product and have at least one measurement of the primary efficacy variable.

For analyses other than efficacy evaluation, such as feasibility evaluation (e.g., recruitment rate, dropout rate, reasons for dropout), the recruitment rate will be calculated as the number of enrolled subjects divided by the total number of screened subjects (%). Dropout rates and

reasons will be analyzed descriptively for both the entire study and each herbal preparation group.

To compare differences between groups for efficacy variables, ANCOVA will be conducted with the assigned group as the factor and the baseline value as the covariate (two-sided  $p < 0.05$ ). If assumptions of ANCOVA (normality, homoscedasticity) are violated or outliers are observed, Ranked ANCOVA will be performed. For categorical data, frequencies and percentages will be calculated, and comparisons between groups will be made using the Chi-square test or Fisher's exact test (if expected frequency is  $\leq 5$ ). Statistical analyses will be conducted using R-software (latest version) or jamovi software (latest version).

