#### **14.4 Analysis of safety variables**

##### **14.4.1 Adverse events**

Adverse events (AEs) are defined as any unfavorable symptoms, signs, or diseases occurring in subjects administered the investigational medicinal product. The number of subjects experiencing all AEs, adverse drug reactions (ADRs), serious adverse events (SAEs), and serious adverse drug reactions (SADRs), along with their incidence rates and 95% confidence intervals, will be presented for each group. Differences between groups will be tested using the Chi-square test or Fisher's exact test. All AEs will be coded using the Medical Dictionary for Regulatory Activities (MedDRA) and presented by system organ class (SOC) and preferred term (PT).

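### Laboratory and vital-sign changes are compared between arms without adjusting for the collected baseline: a valid test, but less precise than the ANCOVA the protocol already uses for efficacy

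*Protocol*

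**What the plan says.** Section 14.4.2 (Laboratory tests, vital signs) gives descriptive statistics before and after treatment, then states: "Changes will be compared between groups using the independent two-sample t-test or Wilcoxon rank-sum test". The Summary has the same instruction: "Compare changes between groups using the independent two-sample t-test or Wilcoxon rank-sum test". The remaining tests in 14.4.2 (paired t, signed-rank, McNemar) are within-group. Neither place mentions a baseline covariate or a confidence interval for the between-group difference.

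For efficacy variables, section 14.1 takes another route: "ANCOVA will be conducted with the assigned group as the factor and the baseline value as the covariate". It falls back to Ranked ANCOVA if assumptions fail or outliers appear.

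The data needed for adjustment are in the schedule. At Visit 0 sites are to "Collect blood samples for laboratory tests and immune and metabolite analysis". Visit 4 repeats AST, ALT, BUN and creatinine (section 11.4.1.4). Vital signs are taken at every visit.

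Adverse events have their own between-group comparison in 14.4.1: "Differences between groups will be tested using the Chi-square test or Fisher's exact test".

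**The concern.** A test on raw change subtracts the whole baseline value. That is optimal only if follow-up rises one-for-one with baseline. If the regression slope of follow-up on baseline is below 1, which under equal SDs means rho below 1, subtraction over-corrects. The difference between arms then carries avoidable variance and part of any chance baseline imbalance.

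Three features of this trial make the point worth a sentence in the plan:

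- Entry allows AST, ALT, BUN and creatinine up to three times the upper limit of normal (section 7), so some participants may start high and regress.
- Laboratory results from within 28 days of the screening visit may be reused (11.4.1.1), and the follow-up sample comes at week 12. A very high baseline-to-follow-up correlation cannot be taken for granted.
- Section 27 lists liver dysfunction among the potential risks, and AST and ALT are measures on which it would show.

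With 50 per arm, a noisier contrast makes a moderate real shift easier to miss.

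**Working it through.** **No figure to reproduce.** The protocol states no power, SD, effect size or detectable difference for any safety variable. The sample size in section 7 is a pilot choice.

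**Inputs from the protocol.** 50 per arm (section 7: "A total of 100 subjects will be recruited, with 50 in the treatment group"), 1:1 allocation (11.3), two-sided 5% tests (14.1).

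**Assumed inputs.** Rho from 0.3 to 0.9; equal SD (sigma) before and after; a true difference of 0.5 sigma. None of these is in the protocol.

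**Variance per participant.**
- Change score: 2(1 − rho)·sigma²
- ANCOVA: (1 − rho²)·sigma²
- Ratio: (1 − rho²) / [2(1 − rho)] = (1 + rho)/2

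**Power (normal approximation).** With s the SD on the relevant scale in units of sigma, SE = s·√(2/50) = 0.2·s and power = Φ(0.5/SE − 1.96). At rho 0.5:
- Change score: s = √1 = 1, SE = 0.200, Φ(2.50 − 1.96) = 70.5%
- ANCOVA: s = √0.75 = 0.866, SE = 0.173, Φ(2.89 − 1.96) = 82.3%

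**Difference detectable with 80% power.** (1.96 + 0.84)·SE.

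| rho (assumed) | Variance ratio | SE reduction | Power, change → ANCOVA | Detectable difference (SD), change → ANCOVA |
|---|---|---|---|---|
| 0.3 | 0.65 | 19% | 56.1% → 74.6% | 0.66 → 0.54 |
| 0.5 | 0.75 | 13% | 70.5% → 82.3% | 0.56 → 0.485 |
| 0.7 | 0.85 | 8% | 89.8% → 93.8% | 0.43 → 0.40 |
| 0.8 | 0.90 | 5% | 97.7% → 98.6% | 0.35 → 0.34 |
| 0.9 | 0.95 | 2.5% | about 100% for both | 0.25 → 0.24 |

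**Simulation check.** Using t-based tests and 4,000 trials per setting, power was 54.8% → 73.1% at rho 0.3, 70.1% → 81.5% at 0.5 and 89.4% → 93.6% at 0.7. These agree with the formula to within about 1.5 points. A separate run of 3,000 trials gave 70.6% → 80.8% at 0.5, 89.3% → 93.4% at 0.7 and 100% for both at 0.9.

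**Validity of the planned test.** In that second run, type I error was 4.5–4.8% for the change-score t-test and 4.5–5.0% for ANCOVA. Both hold their 5% level.

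**Chance baseline imbalance.** One standard error of the baseline difference is √(2/50) = 0.2 SD. The change score carries (1 − rho) × 0.2 of it:
- rho 0.3: 0.14 SD
- rho 0.5: 0.10 SD
- rho 0.7: 0.06 SD
- rho 0.9: 0.02 SD

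ANCOVA removes this shift under the same model.

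**The case against.** The strongest reply is that nothing here is an error. In a 1:1 randomised trial a two-sample test on change is unbiased and keeps its size. Chance imbalance is ordinary sampling error, already covered by the 5% level. That stands, so the point is about precision only.

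Four stronger readings are tempting, and the protocol does not support them:

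- **That this is the trial's only comparison able to show harm.** Section 14.4.1 also tests adverse events, adverse drug reactions and their serious forms between groups. Section 16.1 counts abnormal laboratory results as adverse events, so a harmful ALT or creatinine rise can appear there too. With 50 per arm and assumed event rates, that comparison has about 62% power for 5% versus 20% and 81% for 5% versus 25%.
- **That safety must follow the efficacy model.** Section 14.1 confines ANCOVA to efficacy variables, so the two sections do not contradict each other.
- **That safety alone gets the unadjusted method.** Treatment success (15.1.2, item 13) is an efficacy endpoint built on VAS change without baseline adjustment.
- **That the loss is large.** This depends on rho, which the protocol does not give. Near 0.9 the gain all but vanishes.

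Two technical limits also stand. The variance ratio needs equal SDs before and after. It concerns mean differences, so it does not show that ANCOVA on raw values beats the planned Wilcoxon option for skewed enzymes. The protocol's own Ranked ANCOVA, or a log scale, answers that case better than unadjusted ranks kept as the only alternative. Finally, this is a pilot with no powered safety hypothesis, and no decision rule rests on these p-values.

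**Conclusion.** The point holds as an optional gain in precision, of low severity. The protocol fixes an unadjusted comparison of change for quantitative laboratory and vital-sign data in two places, while holding the baseline values and already specifying a baseline-adjusted method elsewhere.

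For an assumed 0.5 SD difference with 50 per arm, the gain is about 18 power points at rho 0.3, 12 at 0.5, 4 at 0.7, 1 at 0.8 and none at 0.9. Under the stated model ANCOVA is not the less precise choice at any of these values. The planned analysis remains valid, and a result from it would not be wrong.

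**What to change.** In section 14.4.2 and the matching Summary paragraph, replace the two-sample test on change with ANCOVA of the post-treatment value on arm and the participant's own baseline. Apply it to AST, ALT, BUN, creatinine and the vital signs. Name the baseline value, because vital signs are taken at both Visit 0 and Visit 1.

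For skewed values such as AST and ALT, use a log scale or the Ranked ANCOVA fallback already in 14.1. Report the adjusted difference, or the ratio on a log scale, with a 95% CI. Ranked ANCOVA gives a test but no difference in measured units, so where it is used, show the estimate and CI from the unranked or log model beside it.

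The descriptive tables of change can stay. The cost is a few lines of wording. The data and software are unchanged, and the method is already in the protocol.

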#### **15. Criteria, methods, and interpretation of efficacy evaluation**

##### **15.1 Evaluation items and methods**

###### **15.1.1 Primary evaluation variable**

- 1) FSS score after 12 weeks of intervention

FSS scores will be compared between groups after taking 12 weeks of intervention.

**15.1.2 Secondary evaluation variables**

- 1) Final medication adherence  
: The mean, standard deviation, median, minimum, and maximum of the final medication adherence (%) for all subjects after 12 weeks (visit 4 or end of the study) will be presented.
- 2) Differences in final medication adherence between groups  
: The mean, standard deviation, median, minimum, and maximum of the final medication adherence (%) will be calculated and compared between the two groups after 12 weeks of intervention (visit 4 or end of the study).
- 3) FSS scores at visits 2 and 3  
: The FSS scores at each visit will be compared between groups.
- 4) ChFS scores and subscale scores at visits 2, 3, and 4  
: The total score and the subscale scores for physical (items 1-7) and mental health (items 8-11) will be recorded. The total scores and subscale scores at each visit will be calculated and compared between the groups.
- 5) EQ-5D-5L scores at visits 2, 3, and 4  
: The EQ-5D-5L scores will be calculated, and the scores at each visit will be compared between the groups.
- 6) PSQI-K global scores at visits 2, 3, and 4  
: The scores for the 7 components from the PSQI-K questionnaire will be calculated and summed to determine the Global score. The Global scores at each visit will be compared between the groups.
- 7) K-MOCA total and domain scores at visit 4  
: The scores for the 7 domains will be calculated and summed to determine the total score. The total scores will be compared between the groups at visit 4.
- 8) BDI score at visit 4  
: The scores for the 4 domains will be summed to determine the total score, which will be compared between the groups at visit 4.

- 9) DF score, DB score, DF-DB scores at visit 4  
: These scores will be compared between the groups at visit 4.
- 10) Computerized neurocognitive test scores at visit 4  
: The scores for the 5 computerized neurocognitive tests will be compared between the groups at visit 4.
- 11) SPPB test scores for walking Speed, sit-to-stand test, balance test, and total score at visit 4  
: The scores for these 3 tests and the total score will be compared between the groups at visit 4.
- 12) Analysis of recruitment rate, enrollment rate, dropout rate, and reasons for dropout for feasibility evaluation  
: The recruitment rate will be calculated as the number of enrolled subjects divided by the total number of screened subjects (%). The enrollment rate will be calculated as the total number of subjects divided by the total number of screened subjects. The dropout rates and reasons for dropout will be analyzed for the entire study and for each treatment group, and the results will be compared.
- 13) Final treatment success rate  
: Based on existing data regarding the minimal clinically important difference for fatigue, treatment success is defined as a change of 15 points or more on the 0-100 VAS for fatigue symptoms from pre-treatment (visit 1) to post-treatment (visit 4). The frequency and proportion of subjects achieving treatment success in each group will be presented [36] .

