| Inclusion and Exclusion Criteria Evaluation                                | ●       |      |        |        |         |      |
| Random Assignment                                                          |         | ●    |        |        |         |      |
| Prescription and Delivery of Assigned Intervention (Kyungok-go or placebo) |         | ●    | ●      | ●      |         |      |
| Compliance check                                                           |         |      | ●      | ●      | ●       | ●    |
| Combined Medication Evaluation                                             |         |      | ●      | ●      | ●       | ●    |
| 0-100 VAS (Visual Analogue Scale) of Fatigue                               |         | ●    | ●      | ●      | ●       | ●    |
| CHFS (Chalder Fatigue Scale)                                               |         | ●    | ●      | ●      | ●       | ●    |
| EQ-5D-5L                                                                   |         | ●    |        |        | ●       | ●    |
| PSQI- K (Korean version of Pittsburgh Sleep Quality Index)                 |         | ●    |        |        | ●       | ●    |
| K- MOCA (Korean-Montreal Cognitive Assessment)                             |         | ●    |        |        | ●       | ●    |
| BDI (Becks' Depression Inventory)                                          |         | ●    |        |        | ●       | ●    |
| Test for Memorizing Numbers Straight/Reverse                               |         | ●    |        |        | ●       | ●    |
| Computerization Neurocognitive Function Test Score                         |         | ●    |        |        | ●       | ●    |
| SPPB (Short Physical Performance Battery)                                  |         | ●    |        |        | ●       | ●    |
| Adverse Reaction Inspection                                                |         |      | ●      | ●      | ●       | ●    |

● Conducted at that visit ; \*UV: Unscheduled visit (visiting on a day other than the original visit schedule due to adverse reactions, etc.); \* \* Only for women of childbearing age ; \*\*\* To evaluate the selection criteria, we investigated whether fatigue occurred after becoming sick with COVID-19.

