#### **11.4.1.3 Visits 2 and 3 (mid-term visit, Week 4 ( 28 days) $\pm 2$ days, Week 8 ( 56 days) $\pm 2$ days)**

The following tests are conducted during mid-term visits:

- ① Measure vital signs.
- ② After collecting the prescribed herbal medicine from the previous visit, verify the dosage taken.
- ③ Participants follow the investigator's instructions for the following evaluations:
  - Fatigue assessment using FSS.
  - Evaluate fatigue using the Chalder Fatigue Scale (ChFS).
  - Assess fatigue severity using a 0-100 VAS.
- ④ Prescribe a four-week supply of the clinical trial medication based on the random number.
- ⑤ Investigate concomitant medications.
- ⑥ Confirm any adverse reactions after taking the clinical trial medication.

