##### **14.3.2 Secondary efficacy variables**

- 1) Final medication adherence
- 2) Differences in final medication adherence between groups
- 3) FSS scores at visit 2 and visit 3
- 4) ChFS scores and subscale scores at visits 2, 3, and 4
- 5) EQ-5D-5L scores at visit 4
- 6) PSQI-K Global score at visit 4
- 7) K-MOCA total and domain scores at visit 4

- 8) BDI scores at visit 4
- 9) DF score, DB score, and DF-DB score at visit 4
- 10) Computerized neurocognitive test scores at visit 4
- 11) SPPB test scores for walking speed, sit-to-stand test, balance test, and total score at visit 4
- 12) Analysis of recruitment rate, dropout rate, and reasons for dropout for feasibility evaluation
- 13) Treatment success rate in fatigue symptoms after 12 weeks of intervention compared between the treatment and control groups

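### The fatigue VAS is recorded at Visits 1 to 4, but its only efficacy endpoint is a yes/no 15-point change at week 12; adding the score analysis would be a cheap, minor improvement

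*Protocol*

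**What the plan says.** **Collection.** The Schedule Summary marks the row "0-100 VAS (Visual Analogue Scale) of Fatigue" at Visits 1, 2, 3 and 4 and at unscheduled visits. The visit descriptions agree; for Visits 2 and 3, Section 11.4.1.3 has "Assess fatigue severity using a 0-100 VAS".

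**Efficacy use.** The VAS enters the endpoint lists once, as item 13. Section 14.3.2 gives it as "Treatment success rate in fatigue symptoms after 12 weeks of intervention compared between the treatment and control groups". Section 15.1.2 supplies the rule, "treatment success is defined as a change of 15 points or more on the 0-100 VAS for fatigue symptoms", measured from Visit 1 to Visit 4, and ties the cut to a minimal clinically important difference from the literature. It promises counts and proportions per group.

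**The other fatigue scales.** The FSS score at week 12 is primary, and FSS scores at Visits 2 and 3 are secondary. ChFS total and subscale scores are compared at Visits 2, 3 and 4.

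**Methods.** Section 14.1 assigns ANCOVA with the baseline value as covariate to efficacy variables, and the chi-square or Fisher test to categorical data. It also states: "All statistical tests will be two-sided with a significance level of 5" per cent.

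**Purpose.** Section 7, part 3: "The results obtained from this study will be used to calculate the number of participants for future confirmatory clinical trials".

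**The concern.** Cutting a 0-100 scale at 15 points makes a 14-point gain count as nothing and makes gains of 16 and 60 points count the same. It also moves the VAS from the baseline-adjusted ANCOVA to an unadjusted comparison of proportions. The protocol gives no reason for treating this fatigue scale differently from the other two.

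What is at stake is the information passed to the next trial. Section 15.1.2 attaches an important difference to the VAS. For the FSS, Section 11.4.2.13 offers only a severity cut-off of 4, and for the ChFS there is nothing comparable. A future trial sized on the VAS would need a mean difference, a standard deviation and some idea of when the effect appears. The planned outputs contain none of these, although the data will have been collected. A real VAS effect could also fail to show in the responder table.

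**Working it through.** **Inputs from the protocol.** Two-sided alpha 0.05 (Section 14.1). Sample size: "A total of 100 subjects will be recruited, with 50 in the treatment group", so n = 50 per arm; allocation: "The probability of allocation to the treatment or control group is 1:1". Responder cut 15 points.

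**Inputs not in the protocol, so assumed.** SD of VAS change σ = 20 to 30; true difference δ = 10 or 15; mean placebo improvement m = 0 to 15. Change is read as improvement. No power, effect size or response rate is stated, so there is no protocol figure to reproduce.

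**Formulas.**
- Continuous change: power = Φ(δ / (σ√(2/n)) − 1.96).
- Responder rates from the same normal model: pC = 1 − Φ((15 − m)/σ) and pT = 1 − Φ((15 − m − δ)/σ).
- Responder power = Φ([(pT − pC) − 1.96√(2p̄(1 − p̄)/n)] / √([pT(1 − pT) + pC(1 − pC)]/n)), where p̄ is the mean of the two rates.

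**One case in full: σ = 25, δ = 15, m = 5.**
- Continuous: 25√(2/50) = 5; 15/5 − 1.96 = 1.04; power 85%.
- Responder: pC = 1 − Φ(0.4) = 0.345; pT = 1 − Φ(−0.2) = 0.579; p̄ = 0.462. Numerator 0.235 − 1.96 × 0.0997 = 0.039; denominator 0.0969; ratio 0.41; power 66%.

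**All settings (range over m = 0 to 15).**

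| σ | δ | Power, continuous (%) | Power, responder (%) | Gap (points) | n per arm for 80%: continuous vs responder |
|---|---|---|---|---|---|
| 20 | 10 | 70.5 | 46.8–50.6 | 19.9–23.7 | 63 vs 100–110 |
| 20 | 15 | 96.3 | 82.1–84.1 | 12.2–14.2 | 28 vs 46–48 |
| 25 | 10 | 51.6 | 33.5–35.2 | 16.4–18.1 | 99 vs 155–165 |
| 25 | 15 | 85.1 | 64.3–65.7 | 19.4–20.8 | 44 vs 70–72 |
| 30 | 10 | 38.5 | 25.2–26.0 | 12.5–13.3 | 142 vs 223–233 |
| 30 | 15 | 70.5 | 49.6–50.5 | 20.0–20.9 | 63 vs 100–102 |

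The responder endpoint needs 1.57 to 1.75 times the sample. With 40 evaluable per arm, σ = 25 and δ = 15, power is 77% against 55–56%.

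**Check of the formulas.** Simulating a t-test and an uncorrected chi-square test (4,000 runs, five settings with σ = 25 or 30) gave responder power 1 to 5 points above the formula, and a gap of 11 to 18 points.

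**Against the protocol's own ANCOVA, by simulation.** Assumed: baseline mean 65 (SD 16), week-12 SD 22, placebo fall 12, values clipped to 0–100, 3,000 trials per setting.

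| δ | Baseline to week-12 correlation | Responder, chi-square (%) | ANCOVA on score (%) | Gap (points) |
|---|---|---|---|---|
| 10 | 0.3 / 0.5 / 0.7 | 45 / 54 / 73 | 67 / 73 / 88 | 22 / 19 / 15 |
| 8 | 0.3 / 0.5 / 0.7 | 31 / 38 / 55 | 47 / 54 / 72 | 16 / 16 / 17 |

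Repeat runs moved single figures by about 3 points at most. If the baseline SD equals the week-12 SD (both 25, correlation 0.5), the formula gives ANCOVA 93% against 66% for δ = 15, and 64% against 35% for δ = 10. The gap is then wider than in the first table.

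**The case against.** The strongest reply is that little is lost for fatigue as a whole. The primary objective is the FSS, and FSS and ChFS scores already give baseline-adjusted differences and a time course. Section 7 does not say that the confirmatory trial will use the VAS. Item 13 is the last of 13 secondary items in a pilot without a power target. How many participants reach an important change is a legitimate question that a mean difference does not answer. All of this stands, and it keeps the severity low. An unseen SAP might add a VAS summary, but the protocol fixes its own endpoint list and that list has no VAS score.

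A reader might infer more than the documents support:

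- *That the VAS is used only as a yes/no outcome.* This is true of efficacy endpoints only. Section 14.2 also compares the VAS score between groups at baseline.
- *That the Visit 2 and 3 values are thrown away.* No comparison is planned at those visits, but the LOCF rule of Section 14.1 can carry such a value into item 13 when Visit 4 is missing.
- *That the lack of a VAS minimum at entry is a serious flaw.* A participant who enters below 15 cannot improve by 15. With the assumed baseline (mean 65, SD 16), that is (65 − 15)/16 = 3.1 SD below the mean, or about 0.1% of participants.
- *That the power figures show a miscalculation.* They illustrate a general cost of dichotomising. The protocol makes no power claim that they could contradict.

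**Conclusion.** The point holds as a minor, low-cost improvement. Four VAS assessments feed one dichotomised efficacy endpoint, no post-baseline VAS score comparison is planned, and the pilot would give no VAS mean difference or time course for planning. Under the assumed inputs the responder comparison loses roughly 12 to 24 percentage points of power. The direction was the same in every setting tried; the size depends on SDs, correlations and effects that the protocol does not give. It does not follow that the responder rate is wrong, that 100 participants are too few, or that the trial cannot estimate an effect on fatigue.

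**What to change.** In Sections 14.3.2 and 15.1.2, and in the matching list in the Summary, add the fatigue VAS score (0-100) at Visits 2, 3 and 4 as a secondary variable. Analyse it with the ANCOVA of Section 14.1, using the Visit 1 VAS as covariate, and report the adjusted mean difference with its 95% confidence interval at each visit. Keep the 15-point success rate as a supporting result.

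The cost is a few lines of protocol text and analysis code. No new data, visits or participant burden are needed. The downside is three more secondary comparisons, which should be labelled exploratory.
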